## Methods

### Context

In 2016, a Pyrenean cross-cultural structure called Centre for the Promotion of Physical Activity and Health (CAPAS-City) was created to promote PA in 2 cities (Huesca [Spain] and Tarbes [France]). It involves 4 partners: the city councils of Huesca (Spain) and Tarbes (France), and 2 research groups from the University of Zaragoza (Spain) and the University of Pau and Pays de l’Adour (France), respectively. CAPAS-City was funded by the European Regional Development Fund (FEDER) programme for territorial cooperation and sustainable development of cross-border regions (Spain, France, and Andorra in this case) called POCTEFA 2014-2020 (EFA095/15). This center is in charge of developing PA programs and promotional activities that have a beneficial impact on health especially in disadvantaged populations that are more prone to health issues. It is within this framework that this study has been conducted because it is focused on children from disadvantaged neighborhoods.

### Study Design and Population

The study was designed as a randomized controlled trial with 2 arms. In a mid-sized city in the southern part of France, 2 primary schools located in the city’s disadvantaged neighborhood were invited to participate in the study. In France, neighborhoods are classified as disadvantaged on the criterion of income per inhabitant: this income is compared with the average income of the city and that of France. This defines the unfavorable social and economic conditions of the neighborhood and its inhabitants. For example, in the neighborhood considered in this study, the unemployment rate is the highest in the city (26% vs 18%) as well as the prevalence of social housing (49% vs 23%).

Both primary schools agreed to participate in the project. They included children from grade 1 (6 years old) to grade 5 (10 years old) and had never benefited from any intervention in the field of PA. Schools were randomly assigned to either experimental (School A) or control group (School B; see Figure 1). Because the intervention is school based, all the children were included in the study (n=141 for school A and n=148 for school B). Based on studies already published on the same theme, the effects of the intervention are expected to be moderate (standard difference≈0.32, equivalent to an average change in MVPA measurement of 8 minutes per day; SD 18 minutes). In addition, in order to detect a difference of 0.32 with a statistical power of 0.8, a significance level of .05, and a retention rate of approximately 91% with a pre/post comparison, the number of participants should be 70. As a precaution, more children were included. Thus, the number of children enrolled was above the minimum required.

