**Figure 1 figure1:**
[figure not shown]
Flowchart of participants. PA: physical activity; ST: sedentary time.

During the academic year 2016/2017, the following baseline assessments were carried out in these 2 schools: measurements of PA and ST, motors skills, attentional capacities, and academic achievement as well as questionnaires completed by parents. These assessments were carried out in November/December 2016 (T1) and May/June 2017 (T2). Children in both schools had to have parental permission to wear the accelerometer for PA and ST measurement. Motor skills were assessed for all the children at school and their records of academic achievement were collected. The measurements of attentional capacities involved only children in grades 2 and 3.

During the academic school year 2017/2018, the experimental school benefited from a school-based multilevel intervention to increase PA, reduce ST, and make children, parents and teachers aware of the importance of PA for health. This intervention program involved all the children from grade 1 to grade 5. During this interventional year, the same periods of assessment as those carried out at baseline were repeated in November/December 2017 (T3) and May/June 2018 (T4). A final assessment was carried out in June 2019 (T5) after 1 year without any special intervention in the experimental school.

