### Baseline and Follow-Up Assessments

Table 1 reports the number and percentage of children who participated in the assessment times (T1–T2–T3–T4–T5) in the experimental school (School A) and in the control school (School B).

**Table 1 table1:** Children’s participation in baseline, follow-up, and final assessments in the 2 schools.

Measurements			T1	T2	T3	T4	T5

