### Ethics Approval and Consent to Participate

This study has been approved by the Comité de Protection des Personnes Sud Mediterranée III and has been registered at ClinicalTrials.gov under the identifier NCT03983447. Parents/guardians were informed of the intervention project by a written letter. This letter contained a consent form. Afterward, a public meeting with the research team was organized in each school so that parents could come to ask any questions. Then, one of the parents or guardians had to sign the consent form in order to permit the children’s participation in the study. The parents/guardians had to give this consent form to the child, who gave it to the teachers. The researchers collected the consent forms either directly after the meeting or later from the teachers.

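### School B's stated enrolment of 148 contradicts Table 1, and Table 1's changing denominators leave the T5 sample and retention without a fixed base

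*Protocol article*

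**What the plan says.** The enrolment statement under Study Design and Population is that "all the children were included in the study (n=141 for school A and n=148 for school B". It carries no date. The same section describes the schools: "They included children from grade 1 (6 years old) to grade 5 (10 years old", with parentheses closing after the age. It also says "Motor skills were assessed for all the children at school".

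The programme ran for one school year: "During the academic school year 2017/2018, the experimental school benefited from a school-based multilevel intervention". The last wave came a year later: "A final assessment was carried out in June 2019 (T5) after 1 year without any special intervention in the experimental school".

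Baseline and Follow-Up Assessments introduces the counts thus: "Table 1 reports the number and percentage of children who participated in the assessment times". Each cell of Table 1 is a count over a denominator. The text does not say whether the denominator is the school roll, the consented children or something else. The denominators from T1 to T5 are:

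| School | T1 | T2 | T3 | T4 | T5 |
|---|---|---|---|---|---|
| A | 142 | 142 | 135 | 137 | 134 |
| B | 168 | 168 | 154 | 154 | 175 |

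Statistical Analysis plans three things for MVPA and ST: descriptive statistics by school and wave, a 2 schools by 5 times repeated-measures ANOVA, and a chi-square comparison of how many children in each group meet the MVPA recommendation. The chi-square sentence names no wave.

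**The concern.** If every child was included and School B had 148, no School B count can exceed 148, yet several do. A stated sample size is therefore wrong or refers to something the article does not identify, and a reader cannot tell which base participation and retention should be judged against.

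The moving denominators raise a second question: who is in the T5 sample? A grade 1 to 5 school loses its oldest grade each summer and takes in a new first grade. T5 falls one school year after the intervention year. Wave-by-wave T5 summaries for School A could therefore combine children who went through the programme with children who arrived after it. A T5 comparison between schools would then be only partly about whether the effect was maintained.

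**Working it through.** **1. Stated enrolment against baseline denominators.**
- School A: 142 - 141 = 1 child.
- School B: 168 - 148 = 20 children.
- Total: stated 141 + 148 = 289; Table 1 at T1 gives 142 + 168 = 310, a gap of 21.
- 289 does equal the T3 total, 135 + 154, but not its split: School A is 6 too high (141 against 135) and School B 6 too low (148 against 154).

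**2. Are the Table 1 denominators misprints?** Recomputing all 50 percentages, 49 match their printed denominators. The other is a rounding matter (53/134 = 39.55%, printed 39.5). The denominators are the ones actually used.

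**3. School B counts above 148.**

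| Measure | Wave | Count | Count / 148 |
|---|---|---|---|
| Motor skills | T1 | 152 | 102.7% |
| Motor skills | T2, T3, T4 | 153 each | 103.4% |
| Motor skills | T5 | 158 | 106.8% |
| Academic achievement | T1, T2 | 156 each | 105.4% |

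That is seven cells. In School A the largest count is 130, below 141. The choice of base matters: School B accelerometry at T1 is 121/168 = 72.0% as printed, but 121/148 = 81.8% on the stated enrolment.

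**4. Is Table 1 a closed cohort?** School B's denominator rises from 154 at T4 to 175 at T5, so at least 175 - 154 = 21 children were added. This reaches the children measured: 158 had motor tests at T5, so at least 158 - 154 = 4 of them were outside the T4 denominator.

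**5. School A at T5.** The denominator was 137 at T4 (end of the intervention year) and 134 at T5. All 134 can be intervention-year children only if at most 137 - 134 = 3 had left. With g the share of the 137 in grade 5, and no other departures, at most 137 × (1 - g) can remain, so at least 134 - 137 × (1 - g) are newcomers. The article gives no grade counts, so g is an assumption:

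| g | Most who can remain | Fewest newcomers in 134 |
|---|---|---|
| 5% | 130.2 | 3.9 |
| 10% | 123.3 | 10.7 |
| 15% | 116.5 | 17.6 |
| 20% (equal grades) | 109.6 | 24.4 |
| 25% | 102.8 | 31.3 |

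At equal grades, 24.4/134 is about 18%. This takes the denominators to be current school rolls and grade 5 leavers not to have been followed.

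**6. Were the newcomers measured?** At T5 School A has 109 motor tests and 71 accelerometer records. With equal grades, 109 does not exceed the 109.6 who could remain, though having no newcomers among them would mean testing about 99% of those remaining and no newcomer at all. The 71 accelerometer records, which carry the MVPA and ST outcomes, are below the possible number of remaining children throughout the range. Table 1 alone cannot settle it.

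**The case against.** Several points against this are fair.

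- **The 148 is undated and the flowchart is not shown.** It may count the intervention year, since 289 is the T3 total. Six children would then be assigned to the wrong school rather than 20 missing. This does not rescue the figure: 153 School B children had motor tests at T3. Reading 148 as the consented children also fails. The text says all children were included, and the ethics section states that "one of the parents or guardians had to sign the consent form in order to permit the children’s participation in the study", so 152 tested would exceed those permitted.
- **The ANOVA is largely protected.** A child who arrived in 2018-19 has no T1 to T4 values, and a complete-case repeated-measures ANOVA drops that child. This stands. The exposure is in the by-wave descriptive statistics and in any chi-square comparison made at T5.
- **Population definitions are often left to a fuller document.** This also stands, so the absence of a definition is not itself the fault. The fault is that the printed counts contradict each other and have an unstated, changing base.
- **Later arrivals may not be wholly unexposed.** Schoolyard markings, recess and lunch organisation and teacher training act on the school and may have outlasted the programme year. The safe description is children not present for the 2017/2018 programme.

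**Conclusion.** The contradiction for School B is certain from the printed figures: 148 stated, 168 as the baseline denominator, and seven counts above 148. That the sample is open is also certain, with at least 21 children added in School B between T4 and T5. That School A's T5 denominator includes children not present for the programme is very probable but inferred: about 24 with equal grades, about 4 to 31 over the assumed range, given that denominators are rolls and leavers were not followed.

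A reader might infer more, and the documents do not support it:
- That School A's enrolment is impossible too. It is one child off, and no School A count exceeds 141.
- That unexposed children were demonstrably measured in School A at T5. Table 1 does not identify who was measured.
- That an 8-minute effect would shrink to about 6.6 minutes (8 × 0.82). This applies a share of the denominator to an outcome recorded in 71 of 134 children, assumes no effect at all in later arrivals, and carries a pre/post planning value unchanged into the following year.
- That turnover shifted the age mix unequally between schools. No grade or age counts by wave are given.

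This should be corrected, but it does not undermine the main ANOVA if that is run on children with all five waves.

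**What to change.** 1. Correct the enrolment under Study Design and Population so that it agrees with Table 1 and the flowchart. State the date it refers to and what the Table 1 denominators are.
2. For T5 descriptive statistics and any T5 compliance comparison, restrict both schools to children on roll in 2017-18, and show 2018-19 entrants separately.
3. Report retention for the children with T1/T2 data as a separate, fixed base. This is a different group from the 2017-18 roll, which also takes in children who joined in autumn 2017, so the two should not be merged.

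The cost is a recount from existing school rolls, a few sentences of definition and a slightly smaller T5 sample. No new data are needed.

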**Figure 1 figure1:**
[figure not shown]
Flowchart of participants. PA: physical activity; ST: sedentary time.

During the academic year 2016/2017, the following baseline assessments were carried out in these 2 schools: measurements of PA and ST, motors skills, attentional capacities, and academic achievement as well as questionnaires completed by parents. These assessments were carried out in November/December 2016 (T1) and May/June 2017 (T2). Children in both schools had to have parental permission to wear the accelerometer for PA and ST measurement. Motor skills were assessed for all the children at school and their records of academic achievement were collected. The measurements of attentional capacities involved only children in grades 2 and 3.

During the academic school year 2017/2018, the experimental school benefited from a school-based multilevel intervention to increase PA, reduce ST, and make children, parents and teachers aware of the importance of PA for health. This intervention program involved all the children from grade 1 to grade 5. During this interventional year, the same periods of assessment as those carried out at baseline were repeated in November/December 2017 (T3) and May/June 2018 (T4). A final assessment was carried out in June 2019 (T5) after 1 year without any special intervention in the experimental school.

### Baseline and Follow-Up Assessments

Table 1 reports the number and percentage of children who participated in the assessment times (T1–T2–T3–T4–T5) in the experimental school (School A) and in the control school (School B).

**Table 1 table1:** Children’s participation in baseline, follow-up, and final assessments in the 2 schools.

Measurements			T1	T2	T3	T4	T5
**School A**							
		Accelerometry, n/N (%)	91/142 (64.1)	96/142 (67.6)	74/135 (54.8)	45/137 (32.8)	71/134 (53.0)
		Attention, n/N (%)	48/142 (33.8)	49/142 (34.5)	44/135 (32.6)	47/137 (34.3)	53/134 (39.5)
		Motor Skills, n/N (%)	130/142 (91.5)	129/142 (90.8)	125/135 (92.6)	110/137 (80.3)	109/134 (81.3)
		Academic Achievement, n/N (%)	118/142 (83.1)	118/142 (83.1)	105/135 (77.8)	105/137 (76.6)	95/134 (70.9)
		Questionnaire, n/N (%)	90/142 (63.4)	90/142 (63.4)	60/135 (44.4)	60/137 (43.8)	58/134 (43.3)
**School B**							
	Accelerometry, n/N (%)		121/168 (72.0)	116/168 (69.0)	90/154 (58.4)	51/154 (33.1)	86/175 (49.1)
	Attention, n/N (%)		65/168 (38.7)	66/168 (39.3)	58/154 (37.7)	56/154 (36.4)	71/175 (40.6)
	Motor Skills, n/N (%)		152/168 (90.5)	153/168 (91.1)	153/154 (99.4)	153/154 (99.4)	158/175 (90.3)
	Academic Achievement, n/N (%)		156/168 (92.9)	156/168 (92.9)	140/154 (90.9)	140/154 (90.9)	99/175 (56.6)
	Questionnaire, n/N (%)		113/168 (67.3)	113/168 (67.3)	73/154 (47.4)	73/154 (47.4)	57/175 (32.6)

#### Physical Activity and Sedentary Time

GT3X Accelerometers (ActiLife) were used as a valid objective measure to assess the levels of PA and ST [31-33]. These assessments were performed in T1, T2, T3, T4, and T5. Children wore the accelerometer on the right side of the hip, adjusted with an elastic belt, from morning to evening for 8 consecutive days. They removed it to sleep, during the shower, and for aquatic activities. The first day was excluded from the analysis and the data collection was carried out over 5 weekdays and 2 weekend days. The accelerometer had to be worn for at least 10 hours on weekdays and 8 hours on weekend days to be included in the analysis, according to the optimal methodological approach for accelerometry [34]. In addition, if the accelerometer detected at least 10 minutes of activity of 0 counts (cts), allowing this quota of time 1-2 minutes between 0 and 100 cts, this time was determined as “no wear time.” To be considered as representative of children’s usual behavior, wear time had to be valid for at least 3 weekdays and 1 weekend day [35].

For the treatment of accelerometer data, ActiLife version 6.13.3 software (ActiGraph) was used. In order to measure children’s PA, which is described as spontaneous, it is preferable to use epochs of less than 15 seconds which makes it possible to detect more accurately the changes in the child’s PA intensities [36]. Thus, we used 1-second epochs and 5 cut points to establish the different intensity categories [31,37]: sitting time 0-99 cts, standing time 99-300 cts, light PA 301-2295 cts, moderate PA 2296-4011 cts, and vigorous PA 4012 cts and more. To obtain ST, the first 2 cut points were added, and thus the cut point corresponding to ST was 0-300 cts.

In order to better understand the behavioral changes, PA and ST were analyzed within specific periods of the day corresponding to the French cultural children’s schedule: time before school (08:00-08:30); morning and afternoon school time (08:30-12:00 and 14:00-16:00); lunch time (12:00-14:00); after-school time (16:00-19:00); evening time (19:00-21:00). During each of these periods, to be valid, the accelerometers had to be worn for 80% of the standard segment time, with this standard segment time being defined as the length of time in which at least 70% of the participants wore the monitor [31].

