#### Principal Outcomes From Measurements at Baseline Concerning PA and ST

On average, children aged 8-10 spent 67.20 (SD 17.83) minutes in MVPA and 602.97 (SD 36.32) minutes in ST on weekdays. At different periods of the school day, it appeared that (1) during school time, the international recommendation to spend 30 minutes in MVPA were fulfilled by only 26.92% of the grade 2 children and 5.40% of the grade 5 children. In fact, children spent 22-27 minutes in MVPA during school time while they were sedentary for 260-270 minutes. Thus, it was confirmed that school is a highly sedentary place where PA has to be promoted during recess and also during class time through sedentary breaks and active learning strategies. (2) During lunch time, sedentary activities represented 80% of the period (ie, 88-93 minutes of ST against 10-13 minutes of MVPA), suggesting that this period of the school day could be used for children to be more active and less sedentary through an organizational process. (3) Before school, only 2-3 minutes were spent in MVPA while 22 minutes were ST, suggesting that active transportation to school was scarce or that school is very close to home for some children. Thus, children’s and parents’ sensitization to active transportation should be developed.

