**Environmental (level 3): school**					
	Physical and material modifications of the schoolyard			After children’s workshop 4, each class made a design proposal for the schoolyard (marks to be drawn and materials to add for recess). An assessment of these proposals was made with the teachers, the research team, and the representatives of the education department of the town hall, and a choice was made about the implementation of the material required. It led to delineation of different games in the different schoolyards (ie, football field, squares with numbers and letters, snail hopscotch) and acquisition of small material (ie, balls, ropes).	
	Organizational modifications of lunch break			In line with the baseline measurement analyses, actions to reduce ST during lunch break were engaged in cooperation with the canteen’s agents and services. The aim was to move from 90 minutes of sitting time to 50-60 minutes in order to free up time to play in the schoolyard before going back to the classroom. Thus, the research team proposed changes to the organization (ie, 2 canteen services, table-based group organization) from which the educators in charge of lunch time made a choice.	
	Organizational modifications of recess games			The schoolyard was divided into different areas dedicated to specific games during recess and lunch time. This provided an opportunity to have a diversity of games and sports to play together or alone (instead of having one game/sport taking all the schoolyard). The schedule was proposed by the children and supervised by the teachers.	

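### The stated ST analysis has no wear-time term, so a change in wear that differs between schools over time would bias the school × time effect on ST

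*Protocol article*

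**What the plan says.** Under Physical Activity and Sedentary Time, the counts are banded as "sitting time 0-99 cts, standing time 99-300 cts, light PA 301-2295 cts", with moderate and vigorous bands above. ST combines the two lowest bands: "To obtain ST, the first 2 cut points were added, and thus the cut point corresponding to ST was 0-300 cts".

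The same section handles wear time through validity rules. Non-wear is detected and set aside. For a day to count, "The accelerometer had to be worn for at least 10 hours on weekdays and 8 hours on weekend days". For a child to count, "wear time had to be valid for at least 3 weekdays and 1 weekend day". Within fixed clock periods, the device must be worn for 80% of a standard segment.

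The Statistical Analysis section tests effectiveness with a repeated-measures ANOVA, two schools by five assessment times, on MVPA and ST. It names no covariate, no percentage of wear and no standardised day length. The baseline results give ST in minutes throughout: "602.97 (SD 36.32) minutes in ST on weekdays", 260-270 min in school time, and at lunch "88-93 minutes of ST against 10-13 minutes of MVPA".

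For the lunch-break action, Table 2 states: "The aim was to move from 90 minutes of sitting time to 50-60 minutes".

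**The concern.** Minutes of ST can only accumulate while the device is worn, and most worn minutes are sedentary. If one school's children come to wear the device longer or shorter than the other's, ST minutes move even when behaviour does not. The validity rules exclude short records, but two valid records can still differ considerably in length.

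At stake is the school × time effect on ST, one of the two outcomes in the effectiveness analysis. Differential wear could look like an intervention effect or cancel a real one. It is a possibility worth guarding against, because some intervention components concern the device itself. Table 2 lists a workshop on how the accelerometer works, a workshop in which children study their own data, and individual feedback sheets. These could alter wearing habits in the experimental school only. The article gives no data on whether they did.

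**Working it through.** **Inputs.** Weekday ST 602.97 min (SD 36.32) and MVPA 67.20 min (SD 17.83), children aged 8-10, from the baseline results. Clock periods from 08:00 to 21:00, 780 min in all, from Physical Activity and Sedentary Time. Weekday minimum wear 600 min, same section. Planned standardised effect 0.32, set for MVPA, from Study Design and Population. The article gives no mean or SD of wear, so the wear differences below are assumptions.

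**Step 1: does the minimum equalise wear?** Mean ST alone (602.97) exceeds the 600-min minimum, and ST + MVPA = 602.97 + 67.20 = 670.17 min before any light activity. Typical wear is therefore well above the minimum, and nothing in the rules constrains it there.

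**Step 2: share of wear that is ST.**
- The article's own lunch share is 80%, about 95 of 120 min: 95/120 = 79%. Its baseline range gives 88/120 = 73% to 93/120 = 78%.
- School time (330 min): 260/330 = 79% to 270/330 = 82%.
- Before school (30 min): 22/30 = 73%.
- Whole day, if wear is 780 min: 602.97/780 = 77%.

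The range is about 73-82%, treating each period as fully worn.

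**Step 3: shift in ST for an assumed differential change in wear.** Formula: shift = share × change in wear; divide by 36.32 for SD units. It assumes the added or lost wear has the average mix of behaviour.

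| Differential change in wear | Share 73.3% | Share 77.3% | Share 81.8% |
|---|---|---|---|
| 15 min | 11.0 min (0.30 SD) | 11.6 min (0.32 SD) | 12.3 min (0.34 SD) |
| 30 min | 22.0 min (0.61 SD) | 23.2 min (0.64 SD) | 24.5 min (0.68 SD) |

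**Step 4: the same for MVPA.** Share 67.20/780 = 8.6%. 15 min gives 1.3 min (1.3/17.83 = 0.07 SD); 30 min gives 2.6 min (0.14 SD).

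**Step 5: a fixed period.** If the lunch segment is the full 120 min, the 80% rule admits wear from 96 to 120 min. The 24-min span is worth 24 × 0.733 = 17.6 to 24 × 0.818 = 19.6 min of ST. That is the largest gap between two valid full-segment records with the same behaviour, not an expected difference between schools. A shorter standard segment would change it.

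**Step 6: what cancels.** The school × time effect compares changes between schools. With mean wear W, the contamination is share × [(W_A,later − W_A,baseline) − (W_B,later − W_B,baseline)]. A constant school difference, or a change common to both schools, gives zero. No false-positive rate is given here for the interaction test, because it would need the within-child correlation, which the article does not report.

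**The case against.** The strongest reply is that the article is condensed. It never says in words that the ANOVA is run on unadjusted minutes, and a fuller analysis plan might add wear time. That stands as a caution. But the article does commit to a model and gives ST in no other unit of time than minutes. A classical repeated-measures ANOVA also does not readily accept a covariate that changes at each wave, so adjustment would mean a different model or outcome scale.

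Second, the wear rules do real work, especially in the fixed clock periods, where wear can vary only within a narrow range. This stands too: they reduce the problem without removing it. The whole-day minimum also lies far below typical wear. If all the spread in ST came from wear at a 77% share, the SD of wear would be at most about 36.32/0.773 = 47 min, so contrasts such as 600 against 780 min are extremes.

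Third, nothing shows that wear changed differently between schools. A reader might take the fall in accelerometry participation at T4 as such evidence. It is not: Table 1 counts children rather than minutes, and the T4 figures are almost equal (32.8% and 33.1%).

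Fourth, a reader might infer that counting standing within ST makes the lunch action undetectable. The documents do not support that. The 0-300 definition is explicit, and both the intervention description and Table 2 aim to replace sitting with play, which this ST measure can register. What remains is wording: Table 2 calls sitting time what the baseline section reports as ST, standing included.

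**Conclusion.** The point holds for ST as a weakness of the stated model, not as a demonstrated bias. ST makes up roughly 73-82% of wear, the rules do not equalise wear, and the model has no term for it. Under an assumed 15- to 30-min differential change in wear, ST would shift by about 12 to 23 min (0.32 to 0.64 SD at a 77% share). For scale, the lower figure matches the standardised effect of 0.32 planned for MVPA; the article plans no effect size for ST.

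Two stronger readings should be resisted. One is that ST here mainly measures wear time; the article reports no wear times, so only strong dependence can be claimed. The other is that the MVPA result is similarly exposed; its shift under the same assumptions is only 0.07 to 0.14 SD. The conclusion rests on added wear having the average behavioural mix and on wear changing differently in the two schools, neither of which can be checked from the article. The change is worth making because it is nearly free and the analyses were not yet complete when the article was written.

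**What to change.** - Analyse ST with valid wear time as a time-varying covariate in a mixed model with school, time and school × time, or analyse ST as a percentage of wear time. Do so for the whole day and for each period, and treat MVPA the same way for consistency.
- Report mean and SD of valid wear time by school and wave, so readers can see whether differential change occurred.
- Align the wording of the lunch-break aim in Table 2 with the 0-300 definition of ST, or also report the 0-99 band descriptively.

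Cost: minor extra analysis and a few lines of text. Wear time and the separate count bands are already in the accelerometer output, so no new data are needed.
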